## Methods/Design

### Objective

The primary aim of this study is to determine if treatment with BHH10 for 12 weeks results in a greater increase in BMD at L1–4 than those who receive a placebo. The secondary outcomes are:any significant differences in femoral BMD, bone turnover marker levels, DSKI, and EQ-5D score in the group receiving BHH10 compared to the group receiving the placebo after 12 weeks of treatmentto determine if there is a causal relationship between the primary outcome and the DSKI or EQ-5D scorewhether BHH10 is a safe treatment based on laboratory parameters, vital signs, and electrocardiography (ECG).

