### Design and setting

This study is a phase II multicenter, randomized, placebo-controlled clinical trial with two parallel groups. Participants who voluntarily sign informed consent and are eligible for this study will be assigned randomly to one of two groups (the BHH10 or the placebo group) in a 1:1 allocation. Patients will take two tablets of BHH10 or placebo three times daily for 12 weeks.

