#### Primary outcome measurement

The primary outcome will be the change in BMD at the lumbar spine (L1–4) between baseline (visit 1) and 12 weeks after randomization (visit 5). BMD will be examined by dual-energy X-ray absorptiometry. Both participating institutions use the same type of X-ray machine (Lunar Prodigy, GE Medical Systems Lunar, Madison, WI, USA).

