##### DSKI questionnaire score

The DSKI consists of 12 items examining the deficiency syndrome of the kidney [13]. Each item is rated on a three-point symptom scale (0 none, 1 average, and 2 severe) and the total score is used. The change of the DSKI score between randomization (visit 2) and after treatment (visit 5) will be calculated.

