### Health-related quality of life status questionnaire

The EQ-5D is an outcome measurement that is widely used to assess quality of life in patients with osteoporosis [14], and is being used in this trial. This tool contains a five-item description section and a visual analog scale (EQ-VAS) [15]. The five-item description section includes questions on mobility, self-care, usual activity, pain and discomfort, and anxiety and depression. There are three possible responses to each item (no problems, some problems, and severe problems). The participants indicate their present health status by checking the most appropriate score for each of the five items. The EQ-VAS is a self-recorded health score for which the best imaginable health condition is 100 points and the worst is 0 points. The change in the score for each item of the EQ-5D between randomization (visit 2) and after treatment (visit 5) will be measured.

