### Sample size

The primary null hypothesis of this study is that there is no difference in the change in BMD at the lumbar spine (L1–4) between the BHH10 and placebo groups after 12 weeks of treatment. In view of the results of a similar study of herbal medicine in postmenopausal women with osteoporosis [16], a mean difference of 0.047 ± 0.097 between the experimental group and control group was assumed. With a 5% significance level and a power of 80%, it was calculated that a sample size of 66 patients per group would be necessary. Allowing for a dropout rate of 20%, a sample size of 168 participants (84 in each group) has been included.

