### Statistical analysis

The analysis data set will consist of an intention-to-treat data set, a per protocol (PP) data set, and a safety data set. The intention-to-treat data set will include all subjects assigned to each group. The PP data set will include only participants who adhered to the study protocol and completed the clinical study. The minimum compliance rate for participants taking the investigational drugs in the PP data set is 80%. The safety data set will include any participants who were randomly assigned to and received at least one dose of the investigational drug. The intention-to-treat analysis will be the primary analysis and will be compared with the PP analysis in a sensitivity analysis. The last observation carried forward method will be used to manage missing data.

For the descriptive analysis, the two-sample Student’s *t*-test or Wilcoxon rank sum test will be used for continuous data and the chi-squared test or Fisher’s exact test will be used for categorical data depending on whether the data are normally distributed or skewed.

For the confirmatory analysis, the primary efficacy endpoint, the change in BMD at the lumbar spine (L1–4) between baseline and 12 weeks, will be evaluated using Student’s *t*-test or the Wilcoxon rank sum test. The secondary endpoints will be evaluated using Student’s *t*-test or the Wilcoxon rank sum test for continuous data or the chi-squared test or Fisher’s exact test for categorical data. We will perform a regression analysis to examine the causal relationship between the DSKI, EQ-5D, and the primary outcome. All statistical analyses will be performed by a statistician blinded to treatment allocation using SAS (version 9.4, SAS Institute Inc., Cary, NC, USA). A significance level of 5% will be used.

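### A secondary aim asks whether BMD change and DSKI or EQ-5D are causally related, but the planned regression of one post-randomisation outcome on another can show only association.

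*Protocol article*

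**What the plan says.** The Objective section of the protocol article lists among its secondary items: "determine if there is a causal relationship between the primary outcome and the DSKI or EQ-5D" score. The Statistical analysis section returns to it: "We will perform a regression analysis to examine the causal relationship between the DSKI, EQ-5D, and the primary outcome". It names no causal or mediation method and no direction of effect. Nothing elsewhere in the article reduces the wording to association or marks the analysis as exploratory.

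The relevant design facts are these:

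- **Randomisation** (Design and setting): participants "will be assigned randomly to one of two groups (the BHH10 or the placebo group) in a 1:1 allocation". Nothing else is randomised.
- **Lumbar BMD** (Primary outcome measurement): the change runs from visit 1 to visit 5.
- **DSKI** (DSKI questionnaire score): "The change of the DSKI score between randomization (visit 2) and after treatment (visit 5) will be calculated".
- **EQ-5D** (Health-related quality of life status questionnaire): "The change in the score for each item of the EQ-5D between randomization (visit 2) and after treatment (visit 5) will be measured".

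**The concern.** Randomising treatment supports a causal reading of BHH10 on BMD, of BHH10 on DSKI and of BHH10 on EQ-5D. It does not support a causal reading of BMD on DSKI, or the reverse, because women are not randomised to a BMD change or to a DSKI score. Age, comorbidity and compliance could each move both.

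A stated aim of the trial would thus be answered by an analysis that cannot answer it, whatever the p-value. The label matters here. The Background gives the traditional view that kidney dysfunction can lead to osteoporosis, and DSKI scores kidney deficiency. A significant slope presented under a causal heading could easily be taken as clinical confirmation of that view, in a trial meant to lay the ground for phase III.

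**Working it through.** **1. What the design identifies.**

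| Relation | Randomised exposure? | Time order in the changes as defined? |
|---|---|---|
| Treatment → BMD change | Yes | Yes |
| Treatment → DSKI or EQ-5D change | Yes | Yes |
| BMD change ↔ DSKI change | No | No: visits 1 to 5 against visits 2 to 5 |
| BMD change ↔ EQ-5D change | No | No: visits 1 to 5 against visits 2 to 5 |

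The last two rows are the subject of the secondary aim. Adding covariates to a regression changes neither entry in those rows. This step needs no arithmetic, and the conclusion rests on it.

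**2. The planning figures used for scale.** The Sample size section states: "a mean difference of 0.047 ± 0.097 between the experimental group and control group was assumed". It then says: "With a 5% significance level and a power of 80%, it was calculated that a sample size of 66 patients per group would be necessary". The two-sided normal formula gives

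n per group = 2 × [0.097 × (1.960 + 0.842) / 0.047]² = 66.9,

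so 67 against the stated 66. Dividing 67 by 0.8 gives 84 per group and 168 in total, as stated. The planning figures reproduce to within one patient per group, and nothing in this point turns on that difference. The planned standardised effect on BMD change is d1 = 0.047 / 0.097 = 0.485.

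**3. Illustration A: the drug acts on both outcomes, with no link within arms and treatment left out of the model.** The article does not say whether treatment is in the model, so its omission is an assumption. It also gives no DSKI effect, so d2 = 0.3, 0.5 and 0.8 SD are assumed. With 1:1 allocation the correlation induced over both arms is

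r = (d1 × d2 / 4) / √[(1 + d1²/4)(1 + d2²/4)].

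- d2 = 0.3: 0.0363 / √(1.0587 × 1.0225) = 0.035
- d2 = 0.5: 0.0606 / √(1.0587 × 1.0625) = 0.057
- d2 = 0.8: 0.0969 / √(1.0587 × 1.1600) = 0.087

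The chance of a positive two-sided 5% test is taken from the Fisher z approximation, in which atanh(r) × √(N − 3) is the mean of a unit normal and both tails beyond ±1.96 are counted. N = 168 is everyone randomised; N = 132 is 2 × 66.

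| d2 (assumed) | r | N = 132 | N = 168 |
|---|---|---|---|
| 0.3 | 0.035 | 6.8% | 7.3% |
| 0.5 | 0.057 | 10.0% | 11.4% |
| 0.8 | 0.087 | 16.9% | 20.3% |

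A simulation of 5,000 trials per setting agrees: 7.2%, 10.0% and 16.8% at N = 132, and 8.0%, 10.8% and 19.8% at N = 168. With a treatment term the simulated rates return to between 4.4% and 5.4%.

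**4. Illustration B: an unmeasured common cause, with no effect of either outcome on the other.** The correlation it produces is assumed. The simulated percentage of positive tests is:

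| Correlation (assumed) | N = 132 | N = 132, treatment in model | N = 168 | N = 168, treatment in model |
|---|---|---|---|---|
| 0.1 | 21.6% | 21.3% | 25.6% | 24.8% |
| 0.2 | 62.3% | 64.4% | 74.0% | 73.5% |
| 0.3 | 94.0% | 94.1% | 97.6% | 97.6% |

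Adjusting for treatment makes no material difference here. A small p-value is therefore no evidence of causation, even when arm is in the model.

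**The case against.** The strongest reply is that the article condenses a fuller protocol. It says only that a regression will be done, and the model, its covariates and the place of treatment in it properly belong in an analysis plan that is not shown. That stands. A reader might infer that the arms will be pooled without a treatment term, but the article does not say so, and the 7% to 20% range is not an estimate of what this trial will do. Illustration A measures one avoidable mistake, under an assumed DSKI effect, and at the low end the excess over 5% is only about two percentage points.

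A reader might also infer that the trial is bound to report a causal claim. The article speaks of examining and determining, not of demonstrating, so such a report is a foreseeable consequence and not a stated plan.

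The time-order argument has a limit too. The DSKI and EQ-5D sections define the change to be calculated, but they do not rule out questionnaires at visits 3 or 4, and the schedule figure is not shown. The absence of time order is therefore firm for the changes as defined, not for every measurement that may exist.

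None of this rescues the causal wording. It stands in both the aim and the analysis, so it is not a slip. An analysis plan can add covariates, but it cannot make DSKI or BMD change a randomised exposure. Even a formal mediation analysis would rest on untestable assumptions of no confounding, and measurement at the same visit weakens it further.

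**Conclusion.** The point holds as a fault in the stated aim and in the label given to its analysis. As written, a secondary aim asks for a causal conclusion that this regression cannot deliver. That conclusion rests only on what is randomised and on how the three changes are defined, not on either illustration.

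The size of any spurious link cannot be bounded from the document. The illustrated rates depend on the assumed DSKI effects, the assumed omission of treatment and the assumed strength of a common cause. The documents do not support the stronger readings, that treatment is omitted from the model or that a causal finding will certainly be published.

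The reach is limited to one secondary aim. The primary comparison, the randomised comparisons of the secondary outcomes and the sample size are unaffected.

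**What to change.** - In the Objective and Statistical analysis sections, replace the causal wording with 'association' and label the analysis exploratory.
- State that treatment arm is in the model, so that a drug effect on both outcomes does not appear as a link between them.
- Report the adjusted estimate with its confidence interval and draw no causal conclusion from it.

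The direction of the regression, any further covariates and a model form suited to the three-level EQ-5D items can be left to the analysis plan.

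This needs no new data or visits. Recruitment is complete, so the change should be made and dated before unblinding; if unblinding has already happened, the report can still adopt the exploratory label. The downside is a weaker secondary claim.

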### Data monitoring

The clinical research organization, Neoneutra Co., Ltd. (Seoul, South Korea), will conduct regular monitoring to ensure the quality of the data. Its monitors check that the randomly assigned study participants meet the inclusion and exclusion criteria and that the study is proceeding well, and they ensure that the data are adequately recorded in the case report forms. There will be no interim analysis. The study will continue until the 168 participants have completed the study.

### Adverse events

Researchers will record patient-reported symptoms as adverse events on a case report form at each study visit. The causal relationship between the investigational drug and an adverse event will be assessed using a six-point grading scale (1 definitely related, 2 probably related, 3 possibly related, 4 probably not related, 5 definitely not related, and 6 unknown). The severity of the adverse event will be scored on a three-point scale (1 mild, 2 moderate, and 3 severe). If an adverse event is deemed to be caused by the investigational drugs, the dose or frequency can be altered according to the standard operating procedures. There are options for reimbursement through clinical trial insurance if a study participant requires treatment due to an adverse event related to the investigational drugs.

## Discussion

This is the study protocol of a phase II, multicenter, randomized, double-blinded, placebo-controlled trial assessing the effect of BHH10 on postmenopausal women with osteoporosis. This study aims to evaluate the efficacy and safety of BHH10 compared to a placebo after 12 weeks of treatment.

Some clinical studies of the effect of herbal medicine on patients with osteoporosis have been reported. A recent Cochrane systematic review reported that the quality of evidence was generally low and that most included studies (85 of 108) had small sample sizes, ranging from 20 to 120. Therefore, the evidence for the use of herbal medicine in patients with osteoporosis is not conclusive and more rigorously designed studies with larger sample sizes are required [17]. Our study has been designed to take into account the suggestions made for additional research in the Cochrane review. The study will recruit a total of 168 participants to compare the effect of the herbal medicine BHH10 with that of the placebo in postmenopausal women with osteoporosis. The methods used for randomization, treatment concealment, and blinding are at low risk of bias and will be described in detail in the final report. Furthermore, selected biomarkers of bone turnover will be measured to explore the potential advantages of BHH10 in terms of the biochemistry of the bone matrix.

BHH10 includes three herbal medicines: *A. membranaceus*, *C. cassia*, and *P. amurense*. Formononetin, the active ingredient in *A. membranaceus*, has been reported to have a favorable effect on bone formation. One in vitro study reported that formononetin had a positive effect on osteoblasts by increasing the expression of alkaline phosphatase, vascular endothelial growth factor, bone morphogenic protein-2, type I collagen, and osteocalcin in subchondral osteoblasts isolated from normal subjects, and by suppressing their expression in subchondral osteoblasts isolated from patients with arthritis. That study confirmed that formononetin promoted the formation of normal bone cells and inhibited the overexpression of osteogenic genes and cytokines [18]. Furthermore, the *C. cassia* component of BHH10 has been reported to stimulate bone formation in an osteoblastic MC3T3-E1 cell line [19]. Based on the above findings, it is hoped that BHH10 will not only inhibit bone resorption but also promote bone formation.

This trial has some limitations. First, it will not be possible to assess the long-term effects of BHH10 because there will be no follow-up after the 12-week study period. Second, whether the participants take the investigational drugs at the correct time will not be known because no dosage log will be completed.

However, through this rigorous validation, it is hoped that the results of this randomized controlled trial will provide evidence of the efficacy and safety of BHH10 and pave the way for a longer-term confirmatory phase III trial as well as studies of other herbal medicines for postmenopausal women with osteoporosis.

### Trial status

The study was launched on 24 March 2016. The most recent version of the protocol (version 2.7) was approved by the institutional review board on 11 August 2017. Recruitment was completed in April 2018. The results will be published in a peer-reviewed journal.

## Abbreviations

BMD: Bone mineral density
DSKI: Deficiency Syndrome of the Kidney Index
ECG: Electrocardiography
EQ-5D: EuroQol five-dimension questionnaire
EQ-VAS: EuroQol visual analog scale
PP: Per protocol
SAS: Statistical Analysis System
